**Stratified**

**Stratified**

**Selection probability**

**SRS**

Figure 3: Flow diagram of sampling procedure for the study conducted on Epidemiology of Pelvic Organ Prolapse in Sidama National Regional State, Ethiopia, 2022.

## Data Collection Tools and Procedures

The subjective data (self-reported POP symptom) will be collected using a structured, locally validated questionnaire, and the objective data will be collected by measuring the degree of prolapse in centimeters. The data collection tool has 10 parts (sections). Part-I is about socio-demographic characteristics of the participants’, which has eight items. Part-II is focused on the POP-related lifestyle of the participants’, which has six items. Part-III contains 14 items that ask about the Obstetrics and gynecologic history of the participants. Part-IV is about the wealth index of the study participants’ household which has 28 items. Part-V is about POP-SS, which has nine items for baseline assessment and one additional question for end-line assessment that relates to participants’ perceived change of POP-SS after the intervention (PFMT). Part-VI is about the general Pelvic Floor Disability Index, which has three main components and a total of 20 items. Part-VI asks about involuntary leakage of urine, which has four items. Part-VIII is about Obstetric Fistula, which has three items. Part-IX is about objectively measured POP and related measures, which have 14 measurements, of which nine points were measured from in and around the vagina to diagnose POP. The last part (part-X) is about prolapse-related quality of life, which has a total of 20 items divided into nine domains.

The questionnaires used to collect data about socio-demographic characteristics, lifestyle, obstetrics, and gynecologic history were developed from a review of related literature ([23](#_ENREF_23), [26](#_ENREF_26), [37](#_ENREF_37), [39](#_ENREF_39), [55](#_ENREF_55), [61](#_ENREF_61), [62](#_ENREF_62), [79](#_ENREF_79)). It was initially developed in the English version and will be translated into the local language (Sidaamu Afoo) by a native speaker of the language and an expert in maternal or reproductive health. The wealth index questionnaire was adopted from the Ethiopian Demographic and Health Survey in English version ([142](#_ENREF_142)). The tool used to measure Pelvic Organ Prolapse Symptom is a standard tool validated in English, Turkish, Chinese, and Amharic Version ([16](#_ENREF_16), [113-115](#_ENREF_113)). It will be translated into Sidaamu Afoo and evaluated for its psychometric properties (Paper-I) and then the final version will be used. The POP-SS has seven questions with a five-point Likert scale which ranges from zero to four (0= never felt symptom, 1= occasionally, 2= sometimes, 3= most of the time, and 4= all of the time), a higher score indicating severe symptoms ([16](#_ENREF_16)). The participants will be asked how often they have had the following symptoms in the last four weeks: 1) A feeling of something coming down from the vagina? 2) Uncomfortable feeling in the vagina that worsens when standing? 3) A heaviness feeling in the lower abdomen? 4) A dragging feeling in the lower back? 5) A difficulty of emptying the bladder? 6) A feeling of incomplete bladder emptying? 7) A feeling of incomplete bowel emptying? The total score will be calculated by summing up all responses to the seven-question test, and the total score will range from 0 to 28.

Other pelvic floor disorders, including bladder and bowel symptoms, will be assessed using the International Consultation of Incontinence Questionnaire-Short Form (ICIQ-SF) ([143](#_ENREF_143)) and the Pelvic Floor Disability Index (PFDI-20) ([144](#_ENREF_144)). The International Consultation of Incontinence Questionnaire-Short Form (ICIQ-SF) is a four-item, disease-specific tool that assesses the symptoms and quality of life of patients with urinary incontinence. The four items are pertaining to the frequency of leakage, amount of leakage, interference with everyday life, and the perceived cause of leakage. Each item has its own response scale, and the total score is calculated as the sum of the first three items (relating to frequency, volume of leakage, and interference with everyday life). It is treated as a continuous scale with a possible range from 0 to 21, with the higher scores indicating worse symptoms ([87](#_ENREF_87)). The Pelvic Floor Disability Index (PFDI-20) consists of 20 items that contain three subscales: Pelvic Organ Prolapse Distress Inventory-6 (POPDI-6), Urinary Distress Inventory-6 (UDI-6), and Colorectal-Anal Distress Inventory-8 (CRADI-8). Each item has a response of either no (0) or yes (1) depending on the absence or presence of a complaint. If answered yes, the level of discomfort will be rated as 1 = unimportant, 2 = a little, 3 = moderate, or 4 = a lot. Both of these tools will be translated into the local language and translated back to English to check their consistency. The participants will be asked how often they have had the symptoms in the last three months.

To diagnose and quantify the stage of the prolapse objectively, a ruler marked with a centimeter will be used to measure the prolapse of nine points in and around the vagina. In addition, a weight scale and meter marked in centimeters will be used to measure a women’s weight and height to know her Body Mass Index.

Prolapse Quality of Life questionnaires will be used to assess the quality of life among women who have a POP (diagnosed objectively). Health-related quality of life among patients with POP will be measured using the disease-specific tool called Prolapse-Quality of Life (P-QoL) ([90](#_ENREF_90)). It was initially developed in 2005 to measure the severity of prolapse symptoms, its impact on patients’ health-related quality of life, and treatment outcome in English-speaking women. It is prolapse specific, a multidimensional tool with nine domains and 20 items. The domains include general health perception (GHP), prolapse impact (PI), role (RL), physical limitation (PL), social limitation (SL), personal relationship (PR), emotional disturbance (EMO), sleep/energy disturbance (SE), and severity measures (SM). Each domain has its own items/questionnaire each containing four points (0= none/not at all, 1= slightly or little, 2= moderately, and 3= a lot). Each domain has a score of 0 to 100, a higher score indicating poor quality of life. This tool was translated and validated in the Amharic version ([145](#_ENREF_145)). The Amharic version will be translated to Sidaamu Afoo and back-translated to Amharic to check its consistency before actual data collection.

Subjective data will be collected by seven data collectors who were fluent in Sidaamu Afoo, experienced in data collection, and recruited by Hawassa University to collect data from HDSS sites. The data collectors will go to the selected households and collect the data through face-to-face interviews with eligible women (one woman who gave birth at least once or was older than 18 years) from April to June 2022. The interview is mainly focused on socio-economy and demography, obstetrics and gynecology history, wealth index, and symptoms of Pelvic Organ Prolapse. At the end of the interview, all study participants will be invited for a pelvic examination at a nearby health facility; and given an appointment (date and time) irrespective of their symptoms.

Pelvic examinations will be performed by trained staff of Yirgalem Hamlin Fistula Center. On each appointment date, this staff will be assigned to each selected health facility (either health center or hospital) and perform a pelvic examination to diagnose POP by using the Pelvic Organ Prolapse Quantification system ([6](#_ENREF_6)). To perform a pelvic examination, the woman will be informed about the procedure, empty her bladder and bowel. The patient can be positioned in lithotomy position or left lateral. A disarticulated speculum will be inserted into the vagina; and to observe the anterior vaginal wall prolapse, the posterior vaginal wall will be retracted. To observe the posterior vaginal wall prolapse the anterior wall will be retracted during straining or coughing or Valsalva. The descent of the cervix will be evaluated by placing Sims or disarticulated speculum in the vagina and directly observing its descent during Valsalva ([12](#_ENREF_12)).

## Study Variables

The outcome variable of this study is pelvic organ prolapse. The independent variables include: Age in years, mode of delivery, number of childbirth, level of education, body mass index, history of pelvic surgery, trauma, marital status, occupation, heavy lifting, smoking, age at first marriage, age at first delivery, place of delivery, history of instrumental delivery, history of a length of labor more than 24hrs (one day), medical conditions (chronic cough, Diabetes mellitus, hypertension), family history of POP, ethnicity, duration menopause.

## Data Source and Measurement

Data on socio-demography (age, level of education, occupation, permanent place of residence religion, and ethnicity), obstetric and gynecologic history (number of childbirth, age at first marriage and childbirth, mode of delivery) will be recorded based on participants’ self-response to each question.

To diagnose POP symptomatically, the total score of the seven items with a five-point Likert scale will be calculated by summing up all responses and the total score will range from 0 to 28. If the participants' total response score is different from zero, she will be considered as having symptoms of prolapse. The Pelvic Floor Disability Index (PFDI-20) will be measured for each component separately. The average score of each subscale will be computed and multiplied by 25 to convert each subscale score between zero and 100. The overall scale score of the three-component will range from zero to 300. The higher values indicate the worst prolapse symptoms ([144](#_ENREF_144)).

To objectively diagnose POP, there are nine measurement points in the POP-Q system. All are measured at maximum Valsalva, except Total Vaginal Length (TVL) which is measured at rest. Measurements are expressed in centimeters to the nearest 0.5cm. These measures are translated into a staging system as described below (Table 2) ([6](#_ENREF_6), [12](#_ENREF_12), [123](#_ENREF_123)). The nine measurement points in and around the vagina are: Genital Haitus (GH) measured from the middle of the external urethral meatus to the posterior aspect of the hymenal remnant, perineal body (PB) measured from the posterior aspect of the hymenal remnant to the middle of the anal opening, point C is the lowest part of cervix and point D is the insertion of uterosacral ligaments to the cervix. Both points are measured relative to the plane of hymenal remnants. A hymenal remnant is chosen as it is a clearly defined and easily identifiable structure. Total vaginal length is measured from Hymenal remnant to point D (Point C will be used in post-hysterectomy patients). Point Aa is an arbitrary fixed point on the anterior vaginal wall, which is 3cm back from the middle of the external urethral meatus in normal cases. Point Ba is the lowest part of the upper anterior vagina. This point is not a fixed point like Aa. It can be anywhere along the vaginal wall above the first 3cm (Aa). Point Ap and Bp are similar points to Aa and Ba but found on the posterior vaginal wall.

.

Table 2:Stage of Pelvic Organ Prolapse classified according to the Standardized Pelvic Organ Quantification System ([6](#_ENREF_6), [123](#_ENREF_123))

| Stage 0 | Points Aa, Ba, Ap, Bp are all at -3cm and C and D are at greater than /equal to total vaginal length (TVL) -2 cm. |
| --- | --- |
| Stage 1 | The Criteria for stage zero are not met and the leading edge of the prolapse is greater than 1 cm above the hymen. |
| Stage2 | The leading edge of the prolapse is between 1 cm above or below the hymen |
| Stage 3 | The leading edge is greater than 1cm beyond the hymen but less than total vaginal length (TVL) – 2 cm from the hymen |
| Stage 4 | The leading edge of the prolapse is greater than total vaginal length (TVL) -2 cm beyond the hymenal remnant. |

A woman is considered to have POP if she has any stage of prolapse different from stage 0.

Body mass index will be measured at health facilities at the time of pelvic examinations. Participants’ weight will be measured by the kilogram and the height will be measured in meters. Finally categorized as underweight (<18.5Kg/m^2^), normal (18.5 – 25.5Kg/m^2^), overweight (25.5 - 29.9kg/m^2^) and obesity (≥ 30Kg/m^2^) ([146](#_ENREF_146)).

Heavy lifting will be measured by the estimated average hours per day the women carry heavy objects like water, big baby, wood, stone, or types of cement.

History of Pelvic surgery includes any type of surgery that involved pelvic muscle like episiotomy, hysterectomy, or surgery for pelvic tumours.

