## Data Management and Analysis

Data will be entered into Epidata version 3.1 and exported to STATA version 16 for analysis. The entered data will be cleaned and recoded before analysis. If there is any missing data, multiple imputation methods will be used to manage the missing data.

Before performing the main analysis, data will be weighted using the sample selection probability and the weighting class adjustment method to control for selection bias and non-response bias respectively ([147](#_ENREF_147), [148](#_ENREF_148)) based on the auxiliary data collected for the Demographic and Health Survey by Hawassa University.

The nature of the data and its distribution will be checked to identify any special distribution. For categorical data, its frequency will be run and checked for any unusual distribution. For continuous data, both statistical methods (mean, standard deviation, median, Skewness, and kurtosis); and graphical presentations (histogram) will be used to check its normal distribution. A mean and standard deviation will be reported for normally distributed data, while the median and interquartile ranges will be reported for non-normally distributed data.

The primary outcome in this study is the presence of anatomical pelvic organ prolapse, which is pelvic organ prolapse of stage I or more prolapse diagnosed through pelvic examination.

To identify predictors of POP, initially, data stratification will be done to identify possible confounders and effect modifiers ([149](#_ENREF_149)). Variable are considered confounding when their crude result (unadjusted odds ratio) is different from Mantel-Haenszel (M-H) (adjusted odds ratio) on stratified data ([150](#_ENREF_150)). An effect modifier is considered when the odds ratio of a variable is different across the strata.

In addition, the multicollinarity of the independent variables will be checked before the variable is fitted into multivariable logistic regression. In the multiple linear regression model, the variance inflation factor (VIF) > 1 and tolerance statistics < 0.1 show the presence of multicollinarity. The variance inflation factor (VIF) of 1-5 shows moderate multicollinarity, while VIF >5 shows high multicollinarity. In this analysis, variables with high multicollinarity will be omitted from the analysis ([151](#_ENREF_151)).

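### Paper II's stage 0 rule tests C as well as D against a vaginal length measured to D, so a well-supported apex can be staged 1, and stage 0 is undefined after hysterectomy

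*Protocol*

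**What the plan says.** Paper II, Data Source and Measurement, defines the landmarks: "point C is the lowest part of cervix and point D is the insertion of uterosacral ligaments to the cervix". Vaginal length is tied to D: "Total vaginal length is measured from Hymenal remnant to point D (Point C will be used in post-hysterectomy patients". On straining, "All are measured at maximum Valsalva, except Total Vaginal Length (TVL) which is measured at rest".

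Table 2 in that section turns the measurements into stages. Stage 0 needs Aa, Ba, Ap and Bp all at -3 cm and, for the apex, "C and D are at greater than /equal to total vaginal length (TVL) -2 cm". Stage 1 is the residual class: "The Criteria for stage zero are not met and the leading edge of the prolapse is greater than 1 cm above the hymen". The case definition follows directly below the table: "A woman is considered to have POP if she has any stage of prolapse different from stage 0".

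Data Management and Analysis for Paper II states that "The primary outcome in this study is the presence of anatomical pelvic organ prolapse", meaning stage I or more. It also sends any missing data to multiple imputation. Paper III, Eligibility Criteria, admits women with POP-SS symptoms and confirmed stage I-III.

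Hysterectomy is not among Paper II's exclusions, and it is part of a listed exposure: "History of Pelvic surgery includes any type of surgery that involved pelvic muscle like episiotomy, hysterectomy, or surgery for pelvic tumours".

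**The concern.** The apical limit is set relative to TVL, and TVL runs to D. Testing D against that limit measures descent. Testing C against it measures descent plus the length of cervix between D and C. Because both points must pass, the stage 0 criterion is partly a test of cervical length.

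After hysterectomy there is no D. The substitution of C is written for the TVL measurement only, and Table 2 does not carry it into staging. The examiner instructions in Annex II, Part IX, also omit it: they measure TVL to D without qualification, and the form has an ordinary D cell.

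At stake are the prevalence estimate and the risk-factor analysis in Paper II, and to a lesser degree who enters the trial. A woman wrongly placed in stage 1 counts as a case, and any non-zero POP-SS score then completes the stage and symptom criteria for enrolment.

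**Working it through.** There is no stated figure to reproduce, because this is a classification rule. The check uses the protocol's own definitions. Table 2 gives the C/D limit without a sign, so it is read here as height above the hymen.

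**Notation.** s is apical descent on straining and L is the distance from D down to C, both in cm. The protocol gives values for neither.

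- Height of D = TVL - s
- Height of C = TVL - s - L
- Limit = TVL - 2

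**Conditions.**

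- D passes if TVL - s ≥ TVL - 2, that is, s ≤ 2.
- C passes if TVL - s - L ≥ TVL - 2, that is, s + L ≤ 2.

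TVL cancels from both. Since L is positive, the condition on C always decides.

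**Result with a uterus in place.**

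| Descent s | Passes stage 0 (apex) at L = | Fails at L = |
|---|---|---|
| 0 cm | 1, 1.5, 2 | 2.5, 3, 3.5, 4 |
| 1 cm | 1 | 1.5 and above |
| 2 cm | none of the values tested | 1 and above |

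Example: TVL 9, s = 0, L = 3. The limit is 7. D is at 9 and passes; C is at 6 and fails. If all four wall points are at -3 cm, the leading edge is still more than 1 cm above the hymen, so she is stage 1 and a case.

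**If the apex is judged at D.** The condition becomes s ≤ 2 for every L. With a uterus in place this equals a 'C or D' rule, because D is never below C.

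**After hysterectomy.** If TVL and the apical criterion both use C, the condition is again s ≤ 2: it is met at s = 0, 1 and 2 and fails at 2.5. As Table 2 stands, three readings are open:

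- D is absent, so the joint condition is not met and she is a case (the literal reading).
- D is treated as missing and imputed.
- C is used alone.

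Only the third gives the result just shown, and it is not written for staging.

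**Illustrative size, with a uterus in place.** Take L as normal with assumed mean and SD, and s = 0. Readings are to the nearest 0.5 cm, so a recorded L above 2 corresponds to a true L above 2.25. The share failing is P(L > 2.25):

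| Assumed L: mean (SD) | z = (2.25 - mean)/SD | Share failing |
|---|---|---|
| 1.5 (0.5) | 1.50 | about 7% |
| 2.0 (0.5) | 0.50 | 31% |
| 2.5 (0.7) | -0.36 | 64% |
| 3.0 (0.7) | -1.07 | 86% |

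The effect on prevalence is (true stage 0 share) × (share failing). The documents do not give the stage 0 share. For each 10 percentage points of women truly at stage 0, the rule would add 10 × 0.07 = 0.7 to 10 × 0.86 = 8.6 points.

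**The case against.** The strongest reply is that the authors plainly know C stands in for D after hysterectomy, and that examiners are trained and supervised by urogynaecologists in the POP-Q system, so nobody would apply Table 2 mechanically. Part of this stands. The TVL sentence shows the authors' intention, and no text says that an absent D scores as a failed criterion. A reader might infer that every hysterectomised woman is automatically a case, and that this builds in an association between pelvic surgery and prolapse. The documents do not support that: her stage 0 status is undefined, and she is a case only under one of three readings. Any odds ratio for pelvic surgery would also need the share of hysterectomies in that group, which is not given.

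A reader might also infer that many well-supported women are misclassified and that a true prevalence of 56.3% would be inflated on a base of 43.7% at stage 0. That does not follow either. The C-to-D distance is not given, and if it is usually below 2 cm few women are affected. The Literature Review (Prevalence of Pelvic Organ Prolapse) describes the 56.3% as grade two or more, so on that reading the remaining 43.7% includes stage I women, who are cases anyway. Women with any wall point off -3 cm fail stage 0 regardless.

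In the trial, the same staging applies to both arms and symptoms are also required, so the rule creates no bias between arms. Dilution of the effect is possible but not shown.

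Training does not remove the core point. The protocol says the measurements are translated into stages through Table 2, and no other section changes the written rule.

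**Conclusion.** The concern holds for the wording of the rule. By the protocol's own definitions, a woman with a uterus and no apical descent is staged 1 whenever C lies more than 2 cm below D, provided her four wall points are at -3 cm. That feeds Paper II's primary outcome directly and trial entry indirectly. Separately, stage 0 is undefined after hysterectomy.

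The size cannot be derived from the documents. The range of about 7% to 86% of true stage 0 women failing rests entirely on assumed C-to-D distances, zero descent and rounding to 0.5 cm, and should be read as showing sensitivity to that distance. The staging rule should be corrected before the data are classified.

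**What to change.** Reconcile Table 2 with the landmark definitions above it. In the stage 0 row, judge the apex at the point to which TVL was measured: D with a uterus in place (equivalent to 'C or D'), C after hysterectomy. State the sign or direction of the limit. Have the urogynaecologist confirm the wording against the POP-Q standard the protocol cites, and carry the post-hysterectomy provision into the Annex II, Part IX instructions.

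Add one coding rule: after hysterectomy D is recorded as not applicable and is excluded from multiple imputation.

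The cost is a few words in Table 2 and the annex, plus that rule. No new measurement is needed: the examination form already records C, D and TVL, so stages can be assigned from the recorded values.

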## Data Quality Assurance

A two-day training will be given for data collectors about the study objectives, tools, and data collection techniques. The questionnaire used to collect socio- demography data was developed in English from a review of the literature and will be translated to the local language. The POP-SS tool will be translated to the local language Sidaamu Afoo and validated among women diagnosed to have POP at Adare, Bensa, and Yirgalem General Hospitals before the data collection. To ensure clarity of the tools other than the POP-SS, it will be pretested on 5% (41) of the sample at Shebadino woreda. The tool will be checked for clarity and time taken to interview a woman. Based on the result of the pre-test, unclear items will be modified to make it clear. The data collection procedures will be closely supervised (daily).

The professionals who perform pelvic examinations will be trained by urogynaecologists to avoid discrepancies across examiners. Furthermore, they will be supervised during data collection (pelvic examination). To reduce the risk of possible bias in complex sampling data, initially, the sampling procedures are clearly stated in the document and will be implemented accordingly to reduce the risk of sampling bias. Both subjective and objective data will be collected using standardized and locally validated tools. The pelvic examiners will be blinded about the POP-SS and background information of study participants.

